### Data collection among additional eight clusters

Following identical recruitment and screening procedure to that undergone by participants in the original 20 clusters, individuals from the additional eight clusters who provide consent to take part in the study will undergo baseline assessment at their local community centre or in their home. Given the late initiation of this additional sample, participants in the additional eight clusters were enrolled for 18 months. Information on incidence of pneumonia will therefore be collected for 18 months of intervention (including two winter seasons); after this, routine clinic information on pneumonia incidence will be collected on study participants for a further 6 months. The following selected data will be collected at baseline:

1. Basic sociodemographic and economic characteristics

2. Self-reported health status: SF36

3. Self-reported medications currently being taken on a daily basis.

4. Self-reported incidence of, and treatment for, pneumonia within the previous 12 months

5. Self-reported smoking and drinking habits

6. Anthropometry: weight, height and hand-grip strength.

7. Blood pressure measurement: two measurements under sitting conditions separated by five minutes, using a sphygmomanometer.

Ambulatory and hospitalized cases of pneumonia among participants in the additional eight clusters will be identified in an identical manner to that described for the original 20 clusters.

### Costing data

In order to conduct a cost-effectiveness analysis from the societal perspective, information on the costs of these interventions both to the users and the providers is required. These costs should also be supplemented by the costs of treating the disease(s) the intervention(s) aims to avoid and the additional health care the intervention(s) might trigger. These data will be collected over the intervention period using a range of methods.

User costs will be assessed via:

- exit interviews (duration approximately 20 minutes) of study participants to ascertain the costs of accessing the interventions (PACAM and exercise), focussing on the cost of transportation, the time spent accessing the interventions for the beneficiaries and any accompanying persons and whether any lost earnings are reported.

- case-based sampling (duration approximately 45 minutes) in which individuals who have experienced episodes of pneumonia and acute respiratory infections will be identified, contacted and interviewed by telephone, in order to estimate the costs borne by them, and any caregivers. In the interviews, information will be collected on both hospitalised and non-hospitalised patients, including: transportation costs borne by the patient and carer(s); costs of care, number of days out of work (or other productive unpaid activities), income lost by patient and carer(s).

Provider costs will be assessed via:

- defining the types, quantities and prices of the different components required to deliver the interventions (PACAM and exercise) at the health centres and/or community centres by reviewing expenditure and budget records.

- case-based sampling, in which the medical records of individuals who have experienced episodes of pneumonia and acute respiratory infections will be identified, information will be collected on both hospitalised and non-hospitalised patients, including: length of admission; number of emergency room visits; drugs consumed and tests performed.

- analysis of existing data on health centre utilisation rates will be used to measure differences between the trial arms and identify unit costs associated with the different services provided or averted. The costs of providing these services, e.g. diagnoses and treatment for the secondary outcome variables such as diabetes, hypertension, coronary heart disease, stroke, heart failure and fractures, will be estimated based on the MOH reference costs (available on the AUGE website [27]). Because full analysis of the costs of these secondary outcome variables is beyond the scope of the current study, the user costs for these services will be modelled from data collected on pneumonia and acute respiratory infection cases.

The size of samples required for the collection of these data, (for example exit interviews of study participants and review of pneumonia patients' records) will be calculated once the overall variability of the key measures is determined.

## Data handling

### Data acquisition, management and transfer

All study participants will initially be identified by their unique national identification number (RUT). The RUT and other person identifying information will be needed by the project field coordinator and project field staff to ensure adequate monitoring of participants during the study. On transfer of data from the project field coordinator to the data coordinating centre at INTA, the RUT and other person identifying information will be encrypted. Only the project field coordinator and the data manager (based at INTA) will have access to person-identifiable data. Once enrolled onto the study, a unique study number will be assigned to each study participant which will be used on all subsequent study documentation. Only the project field coordinator and the data manager will have access to the coding sheet linking the unique study number to person-identifiable data.

Data collected by project field staff will be securely stored in a locked cabinet by the project field coordinator. All data will be transferred on a weekly basis by the project field coordinator to the data coordinating centre at INTA. Once at INTA, the data will be entered onto computer and the data manager will carry out data validation checks and then feed back any inconsistencies to the project field coordinator for further action as appropriate.

The data coordinating centre at INTA will be responsible for logging all data as they arrive and informing the project field coordinator about any missing data. The data coordinating centre at INTA will also be responsible for the safe storage of encrypted and anonymised data for 20 years after the end of the study.

### Data analysis

Data analysis will be conducted by statisticians at INTA and LSHTM who will be blind to the treatment allocation. The statisticians will prepare interim analyses for the Data Monitoring Committee as required. The interim analyses will focus on safety aspects of the interventions.

At the end of the interventions, primary analyses will be carried out based upon the groups as randomised ("intention to treat"). Results will be presented as appropriate effect sizes with a measure of precision (95% confidence intervals). All analyses will take account of the clustered design. Covariates will be adjusted for in the analysis as necessary. Further exploratory analyses will be based on those participants who fully follow the various treatment protocols ("per-protocol analyses").

Using the results of the trial and the costing information collected, the incremental cost-effectiveness of the interventions will be evaluated. Sensitivity analyses will be performed to assess the robustness of the findings to changes in key economic and epidemiological parameters. This approach will facilitate discussions about the generalisability of the results to other parts of Chile and beyond.

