### 1. Recruitment of health centres (clusters)

#### Original health centre recruitment plan

This pragmatic trial was designed as a public health programme effectiveness study [16] and the interventions were therefore made available through the established health system under standard operating procedures, without the use of resource-intensive extraordinary efforts to secure uptake.

There are 94 health centres in the Santiago Metropolitan area. The study is aimed at low to medium socio-economic status older people, and the nine health centres in high socio-economic status municipalities were therefore excluded. The average number of persons aged 65.0–67.9 per health centre was derived from 1992 census data for each municipality, and small municipalities (those with less than 400 persons of this age group per health centre) were excluded (n = 49) in order to facilitate data collection.

The geographic catchment areas of the remaining 36 health centres in low to medium socio-economic status areas with sufficient older persons were mapped, and following further discussions and site inspections, 15 health centres were excluded because of insufficient interest among health centre staff (self-perception of having heavy burden of work), or infrastructure limitations, for example lack of space to store the nutritional supplement, or no private room to conduct the interviews. Of the 21 remaining health centres, 20 were randomly assigned, using stratified random sampling, to one of the four treatment arms. The remaining health centre was kept in reserve in the event of the withdrawal of a health centre.

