### Nutrition intervention (PACAM)

PACAM was made available to participants aged 65.0–67.9 years at baseline who lived within the defined catchment area of the selected health centres. The programme was provided in its current form as delivered by the Ministry of Health. The primary products of PACAM are the nutritional supplements *Años Dorados *(a cereal-legume and vegetable powdered food) and *Bebida Láctea *(a milk-based powdered drink), 1 kg of each of which is distributed to all eligible individuals every month at the health centre. Detailed nutritional composition of the dietary supplements is provided in Table 1. Compliance with the nutrition intervention is assessed by recording the frequency of collection of the supplements from the health centres, and via specific questions asked at the 12 and 24 month interviews.

**Table 1 T1:** Nutritional composition of the *Años Dorados *and *Bebida Láctea *food supplements used in the Programme for Complementary Food in Older People, Chile, 2007

	**Años Dorados**		**Bebida Láctea**	
	per 100 g	per 50 g serving	per 100 g	per 25 g serving
Energy (kcal)	400	200	406	101.5
Protein (g)	13.0	6.5	18.0	4.5
Total fat (g)	11.0	5.5	10.0	2.5
Carbohydrates (g)	62.3	31.1	61.0	15.3
Total fibre (g)	6.0	3.0	1.0	0.25
				

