### Exercise intervention

Participants were individually invited to attend two physical activity group training sessions per week of one hour each. Training, supervised by CENEX study physical activity instructors, consists of a period of warming up and three levels of chair stands, three levels of modified squats, three levels of step-ups onto a stair, and six sets of 15 repetitions of arm pull-ups using rubber bands of variable resistance. Special exercises were delivered to participants with specific physical limitations. Participants were encouraged to walk to the exercise classes (up to 20 minutes from home) as part of the exercise protocol. Participants unable to attend classes were advised about exercises that could be conducted in their homes. Compliance with the exercise intervention is assessed by recording the frequency of attending the training sessions, and via specific questions asked at the 12 and 24 month interviews.

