### Control group

Participants in the control group received neither the nutritional supplement nor were they invited to attend the exercise intervention. They were however, provided with the same level of general support and information as all other study participants and also underwent identical assessments as all other study participants throughout the study period.

At the end of the study, all study participants will receive educational material on healthy ageing and a certificate in recognition of their participation.

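### The exploratory per-protocol analysis selects on uptake in the active arms with no counterpart in the control arm, so it can show a benefit where there is none

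*Protocol article*

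**What the plan says.** The protocol article, under Data analysis, states that "primary analyses will be carried out based upon the groups as randomised" and calls this intention to treat. It continues: "Further exploratory analyses will be based on those participants who fully follow the various treatment protocols". These are labelled per-protocol analyses.

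Adherence is measured as follows.

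- Nutrition intervention (PACAM): "Compliance with the nutrition intervention is assessed by recording the frequency of collection of the supplements from the health centres", and also "via specific questions asked at the 12 and 24 month interviews".
- Exercise intervention: "Compliance with the exercise intervention is assessed by recording the frequency of attending the training sessions", with the same interview questions added. The section also says: "Participants unable to attend classes were advised about exercises that could be conducted in their homes".
- Control group: "Participants in the control group received neither the nutritional supplement nor were they invited to attend the exercise intervention".

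Under Original health centre recruitment plan, the interventions are offered through routine services "without the use of resource-intensive extraordinary efforts to secure uptake". No expected uptake is given. The article states neither a threshold for full compliance nor a rule for controls.

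**The concern.** The difficulty is the choice of analysis set, and a threshold in a later document would not remove it. Collecting supplements and attending classes are behaviours that exist only where an intervention is offered. Restricting the active arms to people who show them, while controls have no such test to pass, breaks the balance that randomisation gave. Adherers are then compared with a control group that still contains the counterparts of the non-adherers.

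The protocol gives reasons to expect that adherence tracks health. Supplements are collected in person every month, so an illness can interrupt collection. Participants are encouraged to walk to class, while the exercise outcome is walking distance, so people losing mobility may stop attending. With delivery as in routine practice, substantial non-adherence is likely. The result among actual users is also one that policy makers will look at in a programme study. What is at stake is an exploratory result that could suggest efficacy the randomised comparison does not show.

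**Working it through.** The plan gives no figure for the per-protocol analysis, so there is none to reproduce. The check asks what the analysis would show for pneumonia if the supplement had no effect.

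**Inputs from the protocol article (sample size sections)**

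- Hospitalised pneumonia is 5 per 1000, read as per year, with a 5:1 ratio of health centre to hospitalised cases. The total is 5 × (1 + 5) = 30 per 1000 per year, or about 6% over two years.
- The design effect size is a 33% reduction, a risk ratio of 0.67.
- There are 14 clusters of 100 per side (1400 per side), with an intra-cluster coefficient of 0.001.

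**Assumed inputs (the documents give neither)**

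- a = share of the active arm that fully adheres, 0.3 to 0.9.
- k = risk in non-adherers divided by risk in adherers, 1 to 2.

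**Step 1: null risk ratio.** Let adherers have risk q and non-adherers kq. With no effect, the control risk equals the whole-arm average, q(a + (1 − a)k). The per-protocol risk ratio is therefore 1/(a + (1 − a)k). For a = 0.5 and k = 2 this is 1/(0.5 + 0.5 × 2) = 1/1.5 = 0.67.

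**Step 2: chance of a false benefit.** This is the probability of a significant result in favour of the supplement (two-sided 0.05, nominal 2.5% in that direction). It compares 1400 controls with 1400a retained participants, with design effect 1 + (m − 1) × 0.001 for cluster size m. Each cell shows the null risk ratio, then this chance.

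| a | k = 1 | k = 1.25 | k = 1.5 | k = 2 |
|---|---|---|---|---|
| 0.3 | 1.00; 2.5% | 0.85; 9.0% | 0.74; 20% | 0.59; 48% |
| 0.5 | 1.00; 2.5% | 0.89; 8.3% | 0.80; 19% | 0.67; 46% |
| 0.7 | 1.00; 2.5% | 0.93; 6.0% | 0.87; 12% | 0.77; 29% |
| 0.9 | 1.00; 2.5% | 0.98; 3.5% | 0.95; 4.8% | 0.91; 8.3% |

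Simulating 14 versus 14 clusters of 100, with a t-test on cluster proportions and 4000 runs per setting, gave 20% (k = 1.5) and 49% (k = 2) at a = 0.5. It gave 55% at a = 0.3, k = 2. Intention to treat on the same simulated data gave 2.0% to 2.8% throughout.

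**Step 3: factorial comparison.** Pneumonia is compared with versus without nutrition, so the comparator includes exercise-alone clusters, whose participants would be filtered on exercise. Take 5 exercise-alone and 9 control clusters (the eight added clusters split equally, an assumption that fits 14 per side) and the same a = 0.5 and k = 2. The retained comparator has 900 controls at relative risk 1 and 250 exercisers at 0.667. Its average is (900 + 250 × 0.667)/1150 = 0.928, so the risk ratio is 0.667/0.928 = 0.72. With k = 1.5, 0.80 becomes 0.80/0.957 = 0.84. Step 2 uses an unfiltered comparator, so its chances are somewhat too high for the factorial comparison. Step 3 applies one value of a to every nutrition cluster, although the combined arm has two protocols to follow.

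**Step 4: the other direction.** If frailer people adhere more, k is below 1. With a = 0.5 and k = 0.8 the null ratio is 1/(0.5 + 0.4) = 1.11, a spurious harm.

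**Step 5: a randomised alternative.** A complier-average estimate divides the intention-to-treat difference by the difference in uptake. With no effect the numerator has expectation zero whatever a and k are, so the selection above does not enter. The protocol favours this approach: current PACAM users are excluded at entry, and the oldest participants reach 67.9 + 2 = 69.9 years at 24 months, below the programme's entry age of 70.

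**The case against.** The strongest reply is that the trial's conclusions do not rest on this analysis. Intention to treat is primary, the per-protocol work is labelled exploratory, and the nutrition and exercise hypotheses concern people who are offered access. That stands, and it limits the weight of the point.

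A second reply is that the threshold, the control rule and any adjustment may be set in documents not shown. That also stands. The absence of a control rule on outside supplements or exercise is inferred from the article's silence. Such a rule would still not mirror adherence to an offered programme.

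Stronger readings are tempting, and the documents do not support them.

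- A reader might infer that the analysis is certain to favour both interventions. The direction depends on k, which is unknown.
- A reader might infer that full compliance means collecting every month and attending twice a week throughout. The article does not say so.
- A reader might infer that people who exercise at home count as non-compliant. Interview questions on uptake also assess compliance, so this does not follow.
- A reader might infer that two definitions of compliance are mixed, because no follow-up interviews are listed for the eight added clusters. Those clusters have only nutrition or control, and collection frequency can serve as one nutrition measure everywhere.

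Finally, the instrumental-variable approach has weaknesses here. Advice on home exercise is a route that a count of sessions would miss, and participants were told their allocation before consenting. Both must be dealt with in the wording of the fix.

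**Conclusion.** The point holds in a limited form. The primary analysis is unaffected. The exploratory per-protocol analysis selects after randomisation on uptake that has no counterpart among controls, and no choice of threshold cures this.

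Over a = 0.3 to 0.9 and k = 1.25 to 2, the null risk ratio for pneumonia runs from 0.59 to 0.98 against an unfiltered comparator. At a = 0.5 and k = 2 it equals the whole design effect, easing to about 0.72 in the factorial comparison. These figures illustrate what assumed values imply; they do not predict the bias in this trial. With k = 1 there is none, and with k below 1 it reverses. The same selection could affect walking capacity, but no size was worked out for that outcome.

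**What to change.** Replace the per-protocol subset with a complier-average estimate. If the subset is kept, report it beside that estimate and label it a non-randomised comparison that cannot support efficacy. Specify the following in advance.

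- Use cluster allocation as the instrument, keep all enrolled participants, and base inference on clusters.
- Define nutrition exposure from collection records in all nutrition clusters, scaled to months of follow-up because the added clusters run for 18 months and the others for 24. Confirm that these records are kept in the added eight.
- Define exercise exposure as any take-up of the programme, including advised home exercise as captured by the 12- and 24-month compliance questions. Using full adherence as the exposure would breach the exclusion assumption, since partial users may also benefit.
- State the exclusion assumption (allocation acts on the outcome only through uptake), with the caveat that participants were recruited knowing their allocation.

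The cost is mainly analysis wording, because uptake is already recorded. The compliance questions should be checked to confirm that they identify home exercise. Intervals will be wider than for the simple subset comparison.

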### Ethical approval

The protocol for this study has been approved by the Institutional Review Board at INTA, University of Chile, and by the LSHTM ethics committee.

### Project Management Group

A Project Management Group (PMG) will run the trial on a day-to-day basis to ensure the smooth operation of the project. Regular review meetings will be held with other members of the team as appropriate. The responsibilities of the PMG include:

- establishing and monitoring recruitment of participating centres and participants

- distributing and supplying appropriate documentation for the trial

- data collection and management

- data entry and cleaning

- data analysis

- organising and servicing the Data Management Committee.

The PMG will comprise:

[name] (Chair). In Chile: [name], [name], [name], [name]. In the UK/US: [name], [name], [name], [name], [name].

An executive committee will be formed comprised of [name], [name] and [name].

### Data monitoring committee

An independent Data Monitoring Committee (DMC) has been established. The membership comprises Dr. [name] (Head of Institute of Public Health, and Head of Chile Centre for Cochrane Iberoamerica Network), [name] (Professor of Geriatrics, Catholic University Medical School), and Dr. [name] (Permanent Secretary of the committee on Ethics in Human Research at INTA).

The main aim of the independent DMC is to protect and serve study participants. The role of the DMC will be mainly to consider data by group allocation and to make recommendations to the PMG about whether or not the trial should continue as planned. The DMC will particularly focus on safety, and recommendations about stopping for effectiveness would be guided by the stringent Peto-Haybittle rule [28,29]. The DMC will also look at on-going compliance data to check that a difference in exposure is occurring. If a problem were to be detected, this could lead to a recommendation to amend aspects of the protocol. The committee will agree terms of reference and meet once a year or as they determine.

### Publication policy

The primary results of the trial will be published with authorship in relation to participation in the study, subject to the approval of the Executive Committee ([name], [name], [name]) following discussion with the PMG. All publications in specific areas of the study or on methodological aspects may be led by co-investigators in their area of expertise subject to approval by the Executive Committee. The requirements for authorship will follow recommended practice in journal guidelines.

